***Baseline visit 1:***

- Within 1 week of the screening and enrollment visit, all study participants will return to complete a baseline assessment via computer-assisted personal interview (CAPI) (See Appendix E).

- An RA will assist with the administration of the CAPI. This will be conducted in a pre-designated space that affords confidentiality. The CAPI will be interviewer-administered by the RA who will set up the computer, ask questions to the participant and record the responses in the laptop/tablet. Participants recruited inside the DC DOC facilities will complete the “DOC Baseline CAPI” (lasting approximately 30 to 40 minutes) inside the DOC and the “Community Baseline CAPI” (lasting approximately 20-30 minutes) at the post-release visit. Participants recruited in the community will complete the “Combined Baseline CAPI” (lasting approximately 50-60 min) at enrollment.

.

- The CAPI will assess the following domains (see Appendix E for full CAPI content):
- Demographics
- Service Utilization
- Access to Care
- Mental Health
- Sexual Risk Behaviors
- Substance Use
- HCV/HBV/STI/HIV Testing & Treatment
- HIV Medication Adherence
- Post-Release Contact with HIV Healthcare Provider
- Criminal Justice
- Post-Release Concerns

Note: The baseline assessment may occur during the screening, consenting, and enrollment visit, as determined by the facility. In addition, due to operational time constraints in the facility, some of these sections may be administered during the post-release community visit.

***Baseline visit 2:***

Within 1 week of baseline visit 1, participants will complete baseline visit 2, which includes random assignment to the study arm, updates to the study locator information, and medical chart review. Depending on the operational time constraints in the facility and in the community GWU research space (some of which is rented from local CBOs), baseline visit 2 may occur immediately after the screening, consenting, and enrollment process, as determined by the facility or depending on time constraints at the GWU research clinic space.

For participants recruited in the community, a blood draw will be conducted to provide a baseline measurement of plasma viral load and CD4 cell count (baseline only) (see 12-week/24-week study visit section for description about blood draw). Study participants will be randomized at this point to either the 1) intervention arm or 2) the control arm. A 1:1 block randomization scheme will be created using a SAS program to select random assignments. Blocks of 4 will be used to ensure equal population of each group during the course of the study. The study coordinator will manage the randomization list. Prior to the visit, the RA will consult with the study coordinator for the randomized assignments. At the beginning of this visit with the participant, the RA will administer either the intervention (CARE+ Corrections tool) or the control condition to the participant based on their assignment.

- Intervention Arm:

Participants will complete the CARE+ Corrections counseling session, which will last less than 30 minutes. The CARE+ Corrections session will consist of the following:

- The CARE+ Corrections tool is a computerized, one-session motivational interview (for an outline of the CARE+ Corrections tool, see Appendix F: CARE+ Corrections Flow Chart and Excel Spreadsheet).

- The CARE+ Corrections session will be conducted using a laptop computer or tablet with a touch screen and consists of an audio-assisted session in which participants provide responses to questions about demographic characteristics, sexual risk behaviors and attitudes, substance use, mental health, and HIV treatment and adherence.
- After the computerized assessment is completed, the CARE+ Corrections tool will provide tailored feedback based on their responses to the above questions.

- The participants will have the option of selecting up to three skill-building videos on the CARE+ Corrections tool to help support the feedback they received from the initial assessment.
- The participant will work with the assistance of the CARE+ Corrections tool to develop a health promotion plan to support HIV treatment adherence and/or HIV care linkage in the community based on the feedback received from the tool.
- The CARE+ Corrections tool will review the plan steps and then the plan will be printed out.
- The participant will have the option of keeping the printout for him/herself after the visit or having the printout retained by the RA to be given to the participant at the baseline visit 3 (post-release; see below) in order to maintain confidentiality of study participation.
- The RA will be present to assist the study participant if needed and audio headphones will be provided to ensure privacy of responses. The CARE+ Corrections session will last less than 30 minutes

The RA will then review the post-release/follow-up study procedures with the study participant.

Participants recruited inside the facility will receive typical discharge planning services as conducted by the staff at the facility. For example, typical discharge planning for the DOC includes:

- 30 day supply of HIV medications (if patient is prescribed HIV medications)
- Appointment with community provider at Unity Health Care (contracted provider within the DC Jail) or referral to another community HIV provider
- DOC medical records

At this visit, a post-release/follow-up appointment will be made for all study participants. In addition, study participants will be given study materials that provide information about the study clinic location and a toll-free number to call for a reminder of the date and time of the post-release/follow-up appointment. In addition, participants recruited inside the facility will be given a flier reminding them to check in with the study staff upon release (Appendix G: GWU Marketing Materials).

- Control Arm:

Participants will view an educational video on opiate overdose (OD) prevention. Headphones will be provided for viewing. The video will be less than 25 minutes in length. Below is an outline of the information provided in the OD video (see Appendix H: Overdose Prevention Video Script, “Staying Alive on the Outside,” for the video script):

- - - Stories of overdose after release from the correctional setting: release and relapse
    - Statistics on OD upon release
    - Steps to preventing overdose
      - seeking treatment
      - make a plan to stay clean
    - Education about opiate, tolerance and purity, and danger of mixing opiates with other drugs/alcohol
    - Signs of overdose
    - How to respond to an overdose:
      - chest noogies
      - call 911
      - rescue breathing
      - Narcan
      - rescue position

The RA will then review the post-release/follow-up study procedures with the study participant, which includes collection of locator information, description of the post-release visit (see below), and explanation of continued follow-up.

Participants recruited inside the facility will receive typical discharge planning services as determined by the staff at the facility. For example, typical discharge planning for the DOC includes:

- 30 day supply of HIV medications (if patient is prescribed HIV medications)
- Appointment with community provider at Unity Health Care (contracted provider within the DC Jail) or referral to another community HIV provider
- DOC medical records

For participants in the intervention arm, recruited in the community, study staff will provide a cell phone and training on the text messaging portion of the intervention (described below).

At this visit, a post-release/follow-up appointment will be made for all study participants. In addition, study participants will be given study materials that provide information on the study clinic location, 800-number to call and make an appointment. In addition, participants recruited inside the facility will be given a flier reminding them to check in with the study staff upon release (See Appendix G).

Participants recruited in the community will receive a $50 incentive for completion of the baseline visit. Participants recruited in the correctional facility will receive their $50 incentive at the post-release follow-up visit (see below).

- Medical Chart Review: With subjects’ prior consent to the release of their medical records (see Appendix K: Medical Records Release Form) as included in the Informed Consent Form (Appendix D), relevant data will be collected from correctional facility and community provider medical records. Specific measures that will be abstracted include data from the 12 months prior to study enrollment related to HIV clinical care, comorbidities and sexually transmitted infections, and ancillary services (see Appendix I: Medical Records Abstraction Form).

The medical chart review may be conducted inside the DC DOC facility by trained GWU staff. The GWU staff member will use a CARE+ study laptop to abstract participant medical records. The laptop will be stripped down and will have no access to the internet. The study laptop will only be used to enter the information listed in the medical records abstraction form. Once the GWU staff member has entered the medical records data on the laptop, he/she will save the data on a password protected encrypted flash drive and will delete the data from the study laptop. The GWU staff member will transport the flash drive to the GWU offices and store the flash drive in a locked file cabinet within a locked closet to which only GWU study staff will have access.

If medical records are available from correctional facilities and/or community clinics, the medical records will be obtained for data abstraction at GWU.

- Tracking of release dates: Anticipated release date (only for participants recruited inside the correctional facility), sentences and charges, dispositions, incarceration periods and facilities, release statuses, discharge planning and case management services, post-release residential programs, and community health referrals will be provided by staff at the correctional facilities and confirmed during the DC DOC record chart review (see Appendix J: DC DOC Abstraction Form) based on subjects’ prior consent to the release of their DC DOC records (see Appendix L: DC DOC Records Release Form). On a regular basis, study staff will consult with staff at the correctional facilities to confirm the release of study participants. After learning about a participant’s release, the study staff member will begin to attempt to schedule the post-release baseline visit 3 within a two-week period (see Baseline Visit 3—post-release visit).

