***Screening and enrollment visit:***

- An interviewer-administered eligibility screener will be used to determine eligibility of potential study participants (see Appendix E: CAPI Questionnaires—eligibility screener included in baseline CAPI Questionnaires).
- Before administering the eligibility screener, a Verbal Informed Consent will be administered (see Appendix C: Screening Verbal Informed Consent Form). For recruitment conducted inside the DC DOC facilities, once the detainee has provided verbal consent, the GWU study RA will administer the eligibility screener. For recruitment conducted through partnering CBOs or community referrals, GWU staff will ask individuals to confirm their HIV status. For these individuals, GWU staff will also confirm that their release from a correctional facility occurred within the past 6 months. Once HIV positive status and date of release within the past 6 months has been confirmed and the ex-detainee has provided verbal consent, the GWU study RA will administer the eligibility screener.

Eligibility criteria include:

- Currently detained in DC DOC facility or released from the jail, prison, halfway house or other correctional facility 6 months ago or less
- Age ≥ 18
- English speaking
- Able to provide informed consent for research participation
- Anticipated release from jail, prison, halfway house or other correctional facility to the community (or living in the community if recently released ex-detainee)
- Confirmed to be HIV-infected by self-report
- Live in the metropolitan Washington, DC area.
- Able to read at 8^th^ grade level as assessed by brief literacy screen (embedded in Eligibility screener)

Exclusion criteria include:

- Expected release to a restricted setting (or currently living in a restricted setting if recruited in the community) that limits/restricts cell phone use, such as a residential drug treatment program, sober house, half-way house, or similar. If an individual is currently housed in a halfway house or other restricted setting, they may be eligible for recruitment after release from this facility.

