- Detainees or recently released ex-detainees who meet the eligibility criteria will be offered the opportunity to participate in the study. Participation will be voluntary. Detainees who do not meet eligibility criteria or choose not to participate will return to their previous location as determined by the security staff. The standard of care for HIV discharge will not be affected by their refusal to participate.
- Detainees or recently released ex-detainees who elect to participate will complete written, informed consent for study participation with the study research assistant (RA). The informed consent form will be read aloud to the participant (see Appendix D: Informed Consent Forms). A copy of the informed consent will be provided to the participant. For participants recruited inside the DC DOC facilities, the GWU RA will provide the option of leaving their copy with the RA in order to protect confidentiality and receiving it at their next study visit after being released to the community. The RA will maintain a file of completed informed consents at the administrative study office at the Department of Epi/Bio at GWU in a locked file cabinet.
- Consenting study participants will also be asked to provide consent for release of medical records from the DC DOC facilities and any community medical providers that they may come into contact with during the course of the study.
- A study locator form requesting contact information for participants after release in the community will be completed. In the case of recently released ex-detainees the locator form will include participants’ current and anticipated contact information.

For community-recruited individuals, the baseline visit will occur within one study visit as much as possible. However, for individuals recruited inside correctional facilities, the baseline visit may be split across multiple time points if necessary, as determined by constraints of that facility.

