The longitudinal nature of the study (containing a baseline assessment before intervention and two follow-up visits after jail release) will result in repeated assessments of primary outcomes (plasma viral load suppression at Visits 2 and 3) and secondary outcomes (e.g., proportion linking to community HIV care at 30 days, 60 days, 90 days, etc.). These outcomes will be analyzed in the unified framework of generalized linear models (GLMs) with appropriate link functions (logit for dichotomized outcomes, e.g. linkage to care, detectable PVL; identify link for continuous outcomes, e.g. log-transformed PVL; or log link for count outcomes, e.g. # of non-main sexual partners). The setup of GLMs involves relating the expected outcome to a linear function of explanatory covariates, where the explanatory covariates will include a dummy variable encoding the treatment (=1) versus control (=0), dummies for study site and gender, relevant demographic covariates, and their interactions. Depending on the analysis objectives, three GLM model structures will potentially be used: 1) *Marginal models* will be used to analyze population-level intervention effect. Within-individual correlation of repeated measures will be accounted for using Generalized Estimating Equations (GEE),^6,7^ which yields consistent parameter estimates and robust standard error estimates. 2) *Random-effect generalized linear models* will be used to estimate the intervention effect at the individual-level.^8^ For those outcomes with only one follow-up visit, the model will be estimated using conditional logistic regression for binary outcomes or difference-on-difference regression for continuous outcomes for better estimation efficiencies. 3) *Markov transition models* will be used to investigate the intervention effect on the individual behavior change as previously conducted by this group,^9^ and includes the prior history of the outcomes as regression covariates; therefore, the transition model emphasizes more the effect of the intervention on outcome changes given the prior value of the outcome. Using these model setups, we will examine the different aspects of intervention for SA2 and SA3. These models will also allow us to quantify the differences between the two study sites and differences between male and female by testing the interaction between study arm and site, and potentially the interaction between study arm and gender.

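### The research assistant obtains the assignment before the visit; when the whole baseline is one session, that can precede eligibility, consent and the baseline interview

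*Protocol*

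**What the plan says.** The protocol gives one role, the RA, every step from screening to delivery of the assigned condition.

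- Screening and enrollment visit: "the GWU study RA will administer the eligibility screener". Written consent is also completed with the RA, and the form is read aloud.
- Baseline visit 1: "The CAPI will be interviewer-administered by the RA who will set up the computer".
- Baseline visit 2: a 1:1 list is generated in SAS and kept by the study coordinator. "Blocks of 4 will be used to ensure equal population of each group during the course of the study". On timing: "Prior to the visit, the RA will consult with the study coordinator for the randomized assignments". The RA then delivers the assigned condition at the start of that visit.

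The steps may be combined. The screening section says: "For community-recruited individuals, the baseline visit will occur within one study visit as much as possible". Baseline visit 1 notes that the interview may take place at the screening and consent visit. Baseline visit 2 adds that "baseline visit 2 may occur immediately after the screening, consenting, and enrollment process", depending on time constraints in the facility or the clinic space.

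Baseline visit 2 also places randomization within the visit itself, in text that follows the description of the community blood draw.

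**The concern.** Concealment requires that whoever decides on entry cannot know the next arm until the person is irrevocably enrolled. Here the RA is told to obtain the arm ahead of the visit, and in the combined session the visit includes the entry decision.

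Two things are at stake. The first is selective entry. The RA applies the literacy screen, judges capacity to consent, establishes whether the person expects to live somewhere that restricts phone use, and presents the study during consent. Knowing the arm could influence any of these, without intent. The second is the baseline interview, which is interviewer-administered and could be coloured by the known arm.

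The planned analysis does not remove the first problem. The Analysis Plan adjusts for covariates found to be imbalanced and weights for missing follow-up. Neither corrects unmeasured differences between the people let into each arm.

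**Working it through.** **Order of events.** The protocol gives no figure to reproduce here, so the first step is to set the two visit patterns side by side.

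| | Separate visits | One combined session |
|---|---|---|
| Eligibility and written consent | Screening visit | Within the session |
| Pre-intervention interview | Baseline visit 1, within 1 week | Within the session |
| RA consults coordinator | Before baseline visit 2, up to 1 further week later | Before the session, if that is the visit meant |
| Can the RA know this person's arm at consent? | Not through the consultation rule | Yes, on that reading |

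The combined column is the stated aim for community recruits and is permitted in facilities. No section provides sealed envelopes, release after enrolment or any equivalent step.

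The wording within Baseline visit 2 is also hard to reconcile. The assignment is obtained beforehand, the condition is given at the start of the visit, yet randomization is placed within the visit, after the community blood draw is described.

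**Predictability from the block size.** This is the residual risk when visits are separate. Inputs from the protocol: 1:1 allocation, blocks of 4, up to 150 participants. Assumptions: one list, and an RA who knows the block size and every earlier assignment. There are 6 equally likely orders of two A and two B. The RA guesses the arm with more places left in the block.

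| Position in block | Chance it is certain | Chance of a correct guess |
|---|---|---|
| 1 | 0 | 1/2 |
| 2 | 0 | 2/3 |
| 3 | 1/3 (first two alike) | 1/3 × 1 + 2/3 × 1/2 = 2/3 |
| 4 | 1 | 1 |

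- Certain: (0 + 0 + 1/3 + 1)/4 = 33.3%.
- Guessed correctly: (1/2 + 2/3 + 2/3 + 1)/4 = 70.8%, against 50% by chance.
- For 150 participants there are 37 full blocks (148 people) and 2 people in a 38th. Certain: 37 × 4/3 = 49.3. Guessed correctly: 37 × 17/6 + 1/2 + 2/3 = 106.0.

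**What varying the blocks would gain.** In 4,000 simulated lists of 150, guessing the arm that is behind on the running count succeeded 70.7% of the time with blocks of 4, 69.2% with blocks of 4 and 6 mixed, and 68.0% with 4, 6 and 8 mixed. The guess rate barely moves. The benefit is that, with sizes undisclosed, the end of a block can usually no longer be known for certain.

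**The case against.** The strongest reply is that the visit in question is Baseline visit 2, which in the written sequence comes after screening, consent and the interview. Even when the steps run together, visit 2 is described as following enrolment, so an RA could contact the coordinator between the two and comply. The coordinator, not the RA, holds the list. This stands for separate visits. For the combined session it shows that a safe reading exists, but not that the protocol requires it: where one visit is the aim, consulting before the RA meets the participant complies equally well.

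Second, the block figures are upper bounds. Nothing says that RAs are told the block size, and recruitment spans several settings, so more than one RA may share the list and each would see fewer earlier assignments. This also stands.

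Third, the primary outcome is viral load suppression, tested by PCR at another institution on specimens labelled by study ID. That protects measurement of the outcome, but not the make-up of the arms.

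A reader might also infer that the absence of named strata is part of the same defect, because recruitment setting affects visit timing and the analysis includes "testing the interaction between study arm and site". The protocol does not support that. It does not define site as jail versus community or give the share recruited in each, and chance imbalance by setting is not a failure of concealment. The Analysis Plan already puts site in the model and adjusts for imbalanced covariates.

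**Conclusion.** The point holds for the combined session. The consultation rule as worded permits knowledge of the arm before entry is decided, this is the intended pattern for community recruits, and no safeguard is stated. It rests on reading the visit as the whole session, which the text allows but does not compel.

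A reader might infer that allocation is unconcealed throughout the trial, or that a third of assignments are actually known in advance. Neither is shown. With separate visits, the participant's own consent and pre-intervention interview precede the consultation, and the exposure is limited to block predictability: at most 33% certain and 71% guessable, under the assumptions above. The protocol gives no basis for estimating how much selective entry would shift the viral load result, so no size is claimed for that.

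Open delivery of the intervention is unavoidable and is a separate matter.

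**What to change.** Replace the sentence on consulting the coordinator before the visit with a release rule. The coordinator discloses each assignment only once eligibility, written consent, the pre-intervention baseline interview and, for community recruits, the blood draw are recorded. Disclosure is by phone or by the next sequentially numbered, sealed, opaque envelope. Make the sentence placing randomization within the visit agree with this.

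The rule should name only the interview sections given before the intervention. Those recruited in DOC facilities complete the community part of the baseline interview after release, so it cannot precede their assignment.

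As a minor addition, use randomly varying block sizes that are not disclosed to RAs. Stratifying by recruitment setting is optional and not needed to resolve this point.

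The cost is one rewritten procedure and, if block sizes vary, a new SAS list. The existing coordinator can operate it. The drawback is a short wait during the visit, or envelopes to carry.
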